#### Analysis of primary and secondary clinical outcomes

The mean difference in GAD-7 between arms at 8 weeks post-randomisation will be estimated using a mixed-effects linear analysis of covariance (ANCOVA) model with repeated measures and a random intercept at the participant level. We will include as dependent variables the GAD-7 scores at 4 weeks, 8 weeks (primary outcome) and 36 weeks post-randomisation. We will also adjust for trial arm, time, baseline anxiety (GAD-7), weeks of gestation at baseline (a pre-specified baseline variable), the three randomisation stratification variables, and an interaction term for trial arm and time to allow effects to differ over time and be extracted at the different time points. Furthermore, if any baseline variables are found to predict missing outcome data, we will include them as covariates in our model. The mean differences between arms for the GAD-7 at 36 weeks secondary outcome will be estimated using the model described for the primary outcome, with the mean differences between arms for the other secondary outcomes estimated using similar models to those described for the primary outcome.

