#### Follow-up assessments

There are 4 assessments yoked to randomisation that all participants are required to complete: baseline pre-randomisation (T0; 16–28 weeks gestation); 4 weeks post-randomisation (T1; end of intervention for active arm; 20–32 weeks gestation); 8 weeks post-randomisation (T2; 24–36 weeks gestation), and 36 weeks post-randomisation (T3; 12–24 weeks post-birth).

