### Sample size {14}

#### Clinical efficacy sample size

For a two-sided independent samples *t*-test, alpha = 0.05, assuming one baseline and three post-randomisation measures with correlation rho = 0.5 (conservative based on baseline − T2 estimate from Hirsch, Krahe et al., 2021 [27] of rho = 0.42), deflation factor of 0.5 [45], and accounting for 35% attrition (based on online CBT: [46]), we will need 268 participants in total (134 per arm) to have 90% power to detect a GAD-7 effect size of 0.35 (powered slightly conservatively compared to T2 GAD-7 effect size of 0.40 from Hirsch, Krahe et al., 2021 [27]).

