#### Missing data

Where available we will use missing value guidance provided for scales. Where this is not available, we will prorate missing items only when there are no more than 20% missing items by replacing the missing item values with the mean value of the complete items for each individual. Missing baseline data will be simply imputed [52]. Missing outcome data will mainly be dealt with using maximum likelihood methods to fit the mixed models and including baseline variables that predict missing outcome data (to make the missing at random assumption more plausible). We will consider performing multiple imputation for primary and secondary outcomes only if there are post-randomisation variables that are predictive of missingness for these measures, and the proportion of participants with missing values for any of the primary or secondary outcome variables is equal or greater to 10% [53].

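### The random-intercept model for GAD-7 assumes equal variances and correlations across two antenatal visits and one postnatal visit, which can distort the 8-week standard error and, with arm-differential dropout, the estimate

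*Protocol article*

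**What the plan says.** Under Analysis of primary and secondary clinical outcomes {20a}, the model for the primary outcome is a "mixed-effects linear analysis of covariance (ANCOVA) model with repeated measures and a random intercept at the participant level". Its responses are the "GAD-7 scores at 4 weeks, 8 weeks (primary outcome) and 36 weeks post-randomisation". The covariates are arm, time, baseline GAD-7, gestation at baseline and the three stratification factors, plus "an interaction term for trial arm and time to allow effects to differ over time". No baseline-by-time term is listed. The other secondary outcomes get similar models.

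Follow-up assessments places the 4- and 8-week visits (T1, T2) in pregnancy and the last visit after birth: "36 weeks post-randomisation (T3; 12–24 weeks post-birth" on the article's own count.

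Clinical efficacy sample size {14} uses one correlation throughout: "alpha = 0.05, assuming one baseline and three post-randomisation measures with correlation rho = 0.5". It allows for 35% attrition.

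Under Missing data {20c}, "Missing outcome data will mainly be dealt with using maximum likelihood methods to fit the mixed models", with baseline predictors of missingness added as covariates. Multiple imputation will be considered if post-randomisation variables predict missingness and at least 10% of participants lack a value. Section {20a} refers to an approved SAP, which is not shown.

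**The concern.** The random intercept is the only device the article names for dependence within a participant. If the residuals are independent with one variance, the three visits share one variance, and T1–T2 has the same correlation as T2–T3. T1 and T2 are 4 weeks apart in pregnancy. T3 comes 28 weeks after T2, some months after birth. Entry is restricted to GAD-7 below 15 and the rationale expects anxiety to escalate, so a constant spread is not obvious either.

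Two things depend on this structure. The first is the standard error of the 8-week contrast, because the pooled variance borrows from the other visits. The second is how maximum likelihood uses the 4-week score of someone with no 8-week score. That protection under missing-at-random (MAR) dropout relies on the covariance being right.

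**Working it through.** **The plan's own figure.** A two-sample t-test for d = 0.35, two-sided 5% and 90% power needs 173 per arm. Then 173 × 0.5 (the stated deflation factor) = 86.5, rounded up to 87; 87 / 0.65 = 133.8, rounded up to 134; total 268. This matches the article. The point below does not change it.

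**What the model implies.** With intercept variance s_b² and independent residual variance s_e², every visit has variance s_b² + s_e² and every pair of visits has correlation s_b² / (s_b² + s_e²). That is compound symmetry: two covariance parameters, against six for an unrestricted 3 × 3 matrix.

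**Standard error, complete data, ignoring baseline adjustment.** The fitted variance is the average of the three visit variances, so

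model SE / true SE at 8 weeks = √(mean of the three variances / variance at T2).

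The article gives no SDs, so these are assumptions:
- Equal SDs: ratio 1, whatever the correlations.
- SDs 3.5, 4, 3.5: √(13.50 / 16) = 0.92, so 8% too small.
- SDs 3.5, 4, 3: √(12.42 / 16) = 0.88, so 12% too small (11% in the simulation with baseline adjustment).
- T3 SD 1.3 times the others: √((1 + 1 + 1.69) / 3) = 1.11, so 11% too large.

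**Bias.** If T2 is missing and T1 seen, maximum likelihood corrects the observed T2 mean by a slope times the T1 difference between all participants and those still observed. If that slope is too small, then approximately

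bias in an arm's T2 mean = −(true slope − fitted slope) × proportion missing × D,

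where D is the T1 difference, dropouts minus stayers, in SD units. Assume correlations T1–T2 0.65, T2–T3 0.40 and T1–T3 0.40, with equal SDs. The common correlation is (0.65 + 0.40 + 0.40) / 3 = 0.483, and the slope gap is 0.65 − 0.483 = 0.167. With 35% missing, bias = −0.167 × 0.35 × D = −0.058 × D. For assumed D of 0.25, 0.5 and 1 this is −0.015, −0.029 and −0.058 SD. If D is the same in both arms, the two biases cancel in the difference.

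**Simulated fits.** These used 400,000 or 800,000 participants, a true effect of −0.35 SD, an 8-week SD of 4, about 34% missing at 8 weeks and 40% at 36 weeks, and standard errors scaled to N = 268. All SDs (T1/T2/T3 where listed), correlations and dropout slopes are assumptions. SE ratio is model SE over robust SE.

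| Assumed covariance | Dropout | Bias, random intercept (SD) | SE ratio | Coverage | Bias, unstructured (SD) |
|---|---|---|---|---|---|
| Equal SDs, decaying correlations | completely random | 0.001 | 1.00 | 0.951 | 0.000 |
| | MAR, same in both arms | 0.002 | 1.01 | 0.952 | −0.001 |
| | MAR, RELAX arm only | −0.011 | 1.00 | 0.950 | 0.004 |
| SDs 3.5/4/3.5 | completely random | 0.000 | 0.92 | 0.928 | 0.000 |
| | MAR, RELAX arm only | −0.021 | 0.92 | 0.925 | −0.001 |
| SDs 3.5/4/3, less equal correlations | MAR, same in both arms | 0.008 | 0.91 | 0.925 | 0.001 |
| | MAR, RELAX arm only | −0.036 | 0.91 | 0.913 | −0.003 |
| | MAR, opposite in the arms | −0.075 | 0.91 | 0.877 | −0.003 |
| Rising SDs, less equal correlations | completely random | −0.002 | 1.06 | 0.963 | −0.003 |
| | MAR, same in both arms | 0.014 | 1.07 | 0.963 | 0.006 |
| | MAR, RELAX arm only | −0.033 | 1.07 | 0.958 | 0.005 |
| | MAR, opposite in the arms | −0.078 | 1.07 | 0.931 | 0.006 |

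The unstructured fit had an SE ratio of 1.00 and coverage of 0.949 to 0.950 throughout. A second set of fits on other assumed values gave −0.04 to −0.07 SD for RELAX-only dropout driven by the 4-week score, against about 0.01 SD or less with an unstructured covariance. There the model SE was about 11% too large or 8% too small when visit SDs differed.

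**The case against.** The article is a summary. It does not say that the residuals are independent or equally variable, and the SAP may add heterogeneous variances, robust standard errors or a baseline-by-time term. This stands as a limit on what can be asserted, but does not remove the point. Three visits have only six covariance parameters, so an unstructured residual matrix leaves no room for an identifiable random intercept. A SAP using that matrix would have to replace the stated model. Robust standard errors would repair the interval but not a bias from differential dropout.

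A reader might infer that the model yields wrong standard errors and a biased 8-week effect under the attrition the trial expects. The article does not support that. It gives 35% as a total and nowhere says that dropout depends on 4-week anxiety or differs by arm. Bias was near zero under completely random dropout and at most 0.014 SD when dropout depended on earlier scores equally in both arms. The standard error was nearly right whenever the SDs were equal. The direction is not fixed either: the bias favours RELAX if its dropouts are the more anxious at 4 weeks, and the reverse pattern would be expected to reverse the sign.

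The missing-data section also foresees part of the problem. Dropout driven by the 4-week score at 35% would meet both conditions for considering multiple imputation. That is a mitigation, though not a commitment. Finally, a random-intercept ANCOVA is a recognised, parsimonious model that matches the single correlation used for sizing. Parsimony counts for little, however, with three visits and about 174 completers (268 × 0.65).

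**Conclusion.** The point holds as a doubtful and avoidable restriction in the stated primary model; it is not a demonstrated error. The algebra is certain if the residuals are standard. The doubt about equal variances and correlations comes from the article's own visit schedule.

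The size is conditional. The 8-week standard error may be correct or wrong by up to about 11%, too large or too small depending on which visit has the larger spread. The 8-week effect may be biased by about 0.01 to 0.07 SD (3% to 20% of the 0.35 target) if dropout depends on 4-week anxiety in the RELAX arm only, and by up to 0.08 SD in the extreme case of opposite dropout patterns in the two arms. Differential dropout is conceivable, since participants are unblinded and only the RELAX arm has sessions to complete, but the documents do not predict it. All these magnitudes rest on assumed SDs, correlations and dropout slopes.

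**What to change.** For GAD-7 and the secondary outcomes modelled in the same way, replace the participant random intercept by an unstructured residual covariance over T1, T2 and T3. Fit by REML with time as a category and small-sample degrees of freedom (for example Kenward–Roger). A baseline-by-time term is optional and relaxes the single baseline slope. Keep the random-intercept model as the pre-specified fallback if the unstructured fit does not converge. If the SAP already specifies this, change the article's description to match.

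The cost is one line of SAP text and code and four more covariance parameters (six instead of two), plus two more coefficients if baseline-by-time is added. The sample size of 268 is unchanged.

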### Interim analyses {21b}

There are no interim analyses planned.

### Methods for additional analyses (e.G. Subgroup analyses) {20b}

#### Analysis of the mechanistic outcome/mediation analysis

To estimate the extent to which the intention to treat RELAX vs UC intervention effect on anxiety (GAD-7) at 8 weeks (primary) or 36 weeks (secondary) is mediated by interpretation bias (measured using the Recognition Test) at 4 weeks, we will use linear structural equation models estimated using full information maximum likelihood estimation to fit mediation models. We will fit two separate structural equation models for the 8-week and 36-week GAD-7 outcome measures, each fitting two equations: one with the 4-week interpretation bias (RT) mediator as the dependent variable and the other with the GAD-7 outcome as the dependent variable with the RT mediator as an independent variable. Both mediator and outcome models will have arm as a binary independent variable, include the three randomisation stratification factors and the weeks of gestation at baseline variable as independent variables, and will include baseline GAD-7 and interpretation bias (RT) measures as independent variables.

The indirect (or mediated) effect will be calculated in each case by multiplying the estimate of the effect of the intervention on the interpretation bias mediator by the estimate of the effect of interpretation bias on the GAD-7 outcome. For this indirect effect, we will present the percentile bootstrap confidence interval from bootstrapping with 1000 repetitions [51]. We will also present this proportion of the total effect that mediated for each model, calculated as the indirect effect estimate divided by the total effect estimate, multiplied by 100.

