The tendency to engage in repetitive negative thinking (RNT)—worrying about the future and ruminating about the past—is an established risk factor for anxiety. Levels of RNT about a stressful life-event predict subsequent anxiety symptoms [16]. Pregnancy, birth, and adjustment to motherhood are potentially stressful and often characterised by uncertainty, and thus have the potential both to trigger and serve as a focus of RNT. Consistent with this, we have demonstrated a link between perinatal RNT and anxiety in pregnant [17] and postnatal [18] women. Our recent review [19] highlighted consistent evidence of associations between RNT and both depression and anxiety in pregnancy and postpartum. Moreover, worry in pregnancy was a consistent predictor of later (i.e. antenatal and postnatal) anxiety and depression [19].

No study to date has tested the possibility that an early intervention offered to those with RNT in pregnancy could result in lower anxiety later in the perinatal period. This is surprising given that we have effective interventions for RNT in the general population preventing the onset of later psychopathology. For example, Topper et al. [20] found that an intervention targeting RNT in young adults who reported high levels of RNT (i.e. Rumination-focused CBT [21]) resulted in less anxiety 12 months later. As a modifiable risk factor that predicts perinatal psychological distress, we propose that similarly targeting RNT early in pregnancy may result in less escalation of anxiety over the perinatal period. Such an intervention would need to be tailored to the unique experiences and challenges of pregnant women.

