There is evidence that RNT is linked to a negative interpretation bias; that is, the tendency to interpret unclear or ambiguous information in a negative (rather than positive or benign) manner. A negative interpretation bias is a transdiagnostic process characteristic of individuals with a range of emotional disorders [22]. Hirsch and Mathews’ [23] cognitive model of RNT proposes that interpretation bias maintains RNT. In accord with this, there is evidence that RNT is associated with interpretation bias in non-pregnant clinical and non-clinical populations [24], and also in pregnant women [17]. Given the ambiguous nature of stressful situations during pregnancy (e.g. “will the scan show that my baby is ok?”), there are frequent opportunities to make negative interpretations (e.g. “the scan will find something wrong”) that fuel RNT, in turn escalating anxiety.

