#### Baseline assessment

Participants will complete the baseline (T0) assessment via the online RELAX platform, within 10 days of their screening questionnaire, after which time the link will expire. Any participant who has not completed the assessment by that time will no longer be able to do so.^1^ As part of the baseline assessment, participants will first provide informed consent and then proceed to complete the baseline measures:

Demographic variables: date of birth, ethnicity, religion, relationship status, social support, highest level of education, employment status, pre-existing health condition, number of children, estimated due date.

The *Repetitive Thinking Questionnaire (RTQ-10 (trait))* [33] is a 10-item measure of trait RNT. Participants rate the extent to which each item (e.g. “I have thoughts or images about all my shortcomings, failings, faults, mistakes”) is true for them when they are distressed or upset. The highest score possible is 50, indicating the greatest level of RNT. The measure demonstrated high internal consistency in a clinical sample of individuals diagnosed with major depressive disorder, social phobia, GAD or dysthymia (*α* = 0.92, mean inter-item correlation = 0.53 [33], Cronbach’s *α* = 0.90 [28]).

The *Generalised Anxiety Disorder Questionnaire (GAD-7)* [38] is a 7-item measure of anxiety symptoms over the past 2 weeks (e.g. “Feelingnervous, anxious or on edge?”). Items are scored 0–3 where 0 as “not at all,” 1 = “several days,” 2 = “more than half the days” and 3 = “nearly every day.” The GAD-7 has good test–retest reliability (intraclass correlation = 0.83) [38], Cronbach’s *α* = 0.87 [28]).

The *Patient Health Questionnaire (PHQ-9)* [37] measures depressive symptoms over the past 2 weeks. Item ratings are summed to produce a total score from 0 to 27. Participants who score above 1 on item 9: “Thoughts that you would be better off dead or hurting yourself in some way” will not be eligible for inclusion in the trial. The PHQ-9 is a reliable and valid measure of depression severity (*α* = 0.86 in an Obstetrics-Gynaecology population [37], Cronbach’s *α* = 0.84 [28]).

The *Penn State Worry Questionnaire (PSWQ)* [39] measures worry (e.g. “My worries overwhelm me”) and participants rate each statement on a scale of 1 (“not at all typical of me”) to 5 (“very typical of me”). Test–retest reliability is high [39], Cronbach’s *α* = 0.83 [17].

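### The mediation models omit baseline repetitive negative thinking, a measured variable that the protocol's rationale ties to both the mediator and the outcome; a free improvement

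*Protocol article*

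**What the plan says.** The section on analysis of the mechanistic outcome (under Methods for additional analyses {20b}) plans two structural equation models, for GAD-7 at 8 and at 36 weeks. Each has one equation for the 4-week Recognition Test score and one for GAD-7. Besides arm, both equations adjust for the stratification factors and for gestational age at entry. The remaining covariates are given in one clause: "and will include baseline GAD-7 and interpretation bias (RT) measures as independent variables". The indirect effect is the product of the arm-to-bias and bias-to-GAD-7 estimates, with a percentile bootstrap interval. The proportion mediated is also to be reported.

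The Baseline assessment section collects the RTQ-10, which "is a 10-item measure of trait RNT", the PSWQ for worry, and the PHQ-9, which "measures depressive symptoms over the past 2 weeks". None of the three is in the mediation covariate list.

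The Background and rationale {6a} states that "there is evidence that RNT is associated with interpretation bias in non-pregnant clinical and non-clinical populations" and extends this to pregnant women. It also states that "Levels of RNT about a stressful life-event predict subsequent anxiety symptoms" and that "worry in pregnancy was a consistent predictor of later (i.e. antenatal and postnatal) anxiety and depression".

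**The concern.** Arm is randomised; 4-week interpretation bias is not. The b path, from bias to later GAD-7, is therefore an observational regression within arm. It can be read causally only if the common causes of 4-week bias and later GAD-7 are in the model.

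The protocol's own rationale supplies a candidate for such a common cause. If women with more RNT at entry tend to have both a more negative bias at 4 weeks and more anxiety later, beyond what baseline bias and baseline GAD-7 capture, then b is too large. The indirect effect and the proportion mediated are then too large as well. Testing whether interpretation bias mediates the treatment effect is a stated objective, so the estimate should not be left open to a confounder already in the dataset. A larger sample would not help, because this is bias and not imprecision.

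**Working it through.** **1. The plan's own figures.** The mechanistic sample size section gives standardised paths a = 0.5, b = 0.2 and c' = 0.15, and states 83% power for a × b and more than 99% for the a path at N = 268. A Monte Carlo run with 10,000 repetitions, two linear equations and full standardisation gives 83.3% for a × b (delta-method test) and about 100% for the a path. The stated power reproduces, so the question is bias in b and not a wrong figure. The implied true indirect effect is 0.5 × 0.2 = 0.10.

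**2. Which links the document supports.**

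| Baseline variable | Link to interpretation bias | Link to later anxiety | In the mediation models |
|---|---|---|---|
| GAD-7 | – | baseline value of the outcome | yes |
| Recognition Test | baseline value of the mediator | – | yes |
| RNT/worry (RTQ-10, PSWQ) | stated, including in pregnancy | stated | no |
| Depression (PHQ-9) | indirect only, through emotional disorders in general | not stated | no |

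**3. Size of the bias.** The document gives no residual correlations, so a range has to be assumed. Let U be the part of baseline RNT not explained by arm and the listed covariates, scaled to variance 1. Let r be its partial correlation with the 4-week mediator and g its standardised coefficient on GAD-7.

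- Mediator variance given arm: 1 − 0.5² = 0.75. The baseline covariates would lower this somewhat; that is ignored here.
- Bias in b = g × cov(U, M) / var(M) = g × r × √0.75 / 0.75 = r × g / √0.75.
- Estimated indirect effect = 0.5 × (0.2 + bias).
- True total effect = 0.10 + 0.15 = 0.25. It is protected by randomisation, so the true proportion mediated is 0.10 / 0.25 = 40%.

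| r = g (assumed) | Bias in b | Indirect effect (true 0.10) | Overstatement | Proportion mediated (true 40%) |
|---|---|---|---|---|
| 0.05 | 0.0029 | 0.101 | 1% | 41% |
| 0.10 | 0.0115 | 0.106 | 6% | 42% |
| 0.20 | 0.0462 | 0.123 | 23% | 49% |
| 0.30 | 0.1039 | 0.152 | 52% | 61% |

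**4. Check by simulation.** Two simulations with 174 analysed (65% of 268) modelled the baseline measures explicitly. With effects of 0.1, 0.2 and 0.3 on each side, one gave mean indirect effects of 0.106, 0.126 and 0.155, and the other 0.107, 0.128 and 0.169. With the baseline variable in both equations, both returned 0.099 to 0.100. At 0.1 and 0.2 this agrees closely with the formula; at 0.3 the result depends more on the set-up.

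**The case against.** The strongest reply concerns conditioning and direction. A confounder must act on 4-week bias given baseline bias and on later GAD-7 given baseline GAD-7, and both baselines are already in the equations. The theory cited in the Background runs from interpretation bias to RNT, and its evidence on the two is an association. If baseline bias drives baseline RNT, adjusting for baseline bias closes much of the route. Nor does the Background say that worry predicts later anxiety after adjustment for baseline anxiety. The entry criteria (RTQ-10 of at least 28, GAD-7 below 15, no symptoms consistent with a current psychiatric diagnosis) narrow the ranges further. All of this stands as a reason to expect an effect towards the low end of the table.

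It does not remove the point. One 12-scenario baseline bias score, measured with error, together with baseline GAD-7, need not carry all of RNT's influence. RTQ-10 can still run from 28 to 50, and PSWQ has no entry limit. Over-adjustment is not a risk, because a variable measured before randomisation cannot block a path from 4-week bias through later RNT to anxiety.

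A statistical analysis plan exists and is not shown. It may add a sensitivity analysis, and the absence of one here is not held against the protocol article. The point is about the covariate list that the article does state. The article's provision for adding baseline predictors of missing outcome data belongs to the clinical outcome model and serves another purpose.

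Three stronger readings are tempting and not supported:

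- **That the protocol makes the same case for depression.** It does not. Depression appears as something that RNT accompanies or predicts, and bias is tied only to emotional disorders in general.
- **That the trial's only test of mechanism is at risk.** The Mechanistic outcome section makes the randomised arm difference in 4-week bias the primary mechanistic outcome, and this issue does not touch it.
- **That false claims of mediation would be common.** A simulated false-positive rate of about 25% with no true mediation needs residual effects of 0.3 on both sides, larger than the planned b of 0.2. At 0.1 the rate was 6.1% against 5.6% with adjustment, a difference close to simulation error (standard error about 0.4 points per rate with 4,000 runs). These rates also come from a joint-significance test, not the planned percentile bootstrap.

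**Conclusion.** The point holds in a limited form. The stated mediation models omit a measured baseline variable that the protocol's rationale associates with both the mediator and the outcome, on the one path that randomisation does not protect. Only residual confounding is in question, and the document does not allow its size to be derived. Under assumed residual effects of 0.05 to 0.20 on each side, acting in the same direction, the indirect effect of 0.10 would be overstated by about 1% to 23%. The figure of about 50% needs 0.30 on both sides, which is unlikely after the planned adjustment.

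The consequence is confined to the mediated effect and the proportion mediated. The primary GAD-7 comparison, the arm difference in interpretation bias and the stated power figures are unaffected. This is a free improvement and not an error that undermines the trial.

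**What to change.** In the section on analysis of the mechanistic outcome, add baseline RTQ-10 as a continuous covariate to both the mediator and the outcome equation of the 8-week and 36-week models, keeping every covariate already listed. Baseline PHQ-9 may be added in the same way on general grounds. PSWQ is optional, since it overlaps with RTQ-10. State the choice before the mediation results are seen, so that the adjustment set cannot be picked after the fact.

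The cost is one sentence and one or two extra terms per equation. The data are already collected, and the plan already covers missing baseline values by simple imputation.
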